## Abstract

**Background:**

Among women at high risk for HIV and other sexually transmitted diseases (STIs), gender and economic issues limit the impact of behavioral prevention strategies. Women in Kazakhstan with dual risks of sex trading and drug use face elevated risk for HIV and STIs and may benefit from an economic empowerment intervention which combines HIV-risk reduction (HIVRR) education with financial skills-building and asset-building to promote reduced reliance on sex trading for income.

**Methods/design:**

The study employs a two-arm, cluster-randomized controlled trial (c-RCT) design. We will use cluster randomization to assign 350 women in approximately 50 cohorts to a traditional four-session HIV-risk-reduction intervention combined with a six-session financial literacy intervention, enrollment in a 24-session vocational training program and receipt of matched savings (HIVRR+MF); or to the four-session HIV-risk-reduction intervention alone (HIVRR). Repeated behavioral and biological assessments will be conducted at baseline, then at 6, 9, and 15 months post randomization/session 1.

**Discussion:**

This study responds to an identified need in the academic literature for rigorous testing of structural interventions, including combination microfinance and HIV-prevention interventions.

**Trial registration:**

ClinicalTrials.gov, ID: NCT02406482. Registered on 30 March 2015.

**Electronic supplementary material:**

The online version of this article (10.1186/s13063-018-2566-y) contains supplementary material, which is available to authorized users.

## Background

While the HIV epidemic in Kazakhstan has remained concentrated among high-risk populations since its beginnings, a recent shift from parenteral to heterosexual transmission highlights the increased risk of HIV transmission to, and by, female sex workers (FSW). HIV prevalence continues to rise among FSW throughout the Central Asian region, yet there has been limited research and exposure to evidence-based HIV-prevention interventions for this population [1]. As of 2014, there were an estimated 19,600 FSW in Kazakhstan, yet only 15 of 93 registered HIV service non-governmental organizations (NGOs) throughout the country served FSW [2]. One systematic review and meta-analysis has estimated that in low- and middle-income countries like Kazakhstan, sex workers have 13.5 times the odds of contracting HIV compared to all women of reproductive age [3]. While official estimates put the prevalence of HIV among FSW in Kazakhstan at 1.3% [4], HIV prevalence is higher among FSW who use both injection and non-injection drugs than among FSW who do not share these additional risks [1]. Drug-using female sex workers are at the greatest HIV risk and the least likely to have access to testing, care or treatment services – they operate at the lower end of the market, are more often street-based, and are typically much poorer than non-drug-using FSW [2]. These women’s low social and economic standing may not only drive entry into sex work, but may make them financially dependent on paying or intimate male partners for living and drug expenses, less able to negotiate safe sex or safe injection practices, and may increase their risk for physical or sexual violence [5–7]. Stigma against both sex work and drug use and aggressive policing may limit their access to health services including drug treatment as well as legal recourse, and may subject them to sexual coercion and violence from police themselves [6, 8]. Furthermore, in Central Asia, few women who use drugs have been reached through evidence-based HIV or harm-reduction interventions, and most local HIV or drug treatment programming has not met their unique needs [9].

Given how these risks are rooted in women’s low economic and financial standing, promoting women’s economic empowerment may provide structural protection from HIV. Structural approaches to HIV prevention are characterized by Gupta et al. (2008) as those which address the physical, social, economic, and policy environments which create vulnerability to HIV [10]. This includes programs which seek to alleviate the economic inequalities faced by high-risk women [11–13]. “Microfinance” has been identified as an important structural intervention for HIV prevention and improved access to testing, care, and treatment [13–15]. The term microfinance covers an array of programs and policies, including financial literacy education, vocational training, conditional or unconditional cash transfers, formal or informal microcredit or lending, small business development, and asset-building through savings programs. In Kazakhstan, microfinance played a crucial role in the establishment of private enterprise after the fall of the Soviet economic system [16]. Microfinance programs usually include a collaboration between a banking institution and an NGO or United Nations agency, offering business guidance such as product development and marketing in combination with a microloan [16]. However, we found no microfinance programs that either target or incorporate drug users or sex workers. Microfinance lenders may consider these risk groups too unstable or unreliable for loans, and stigma against these risk groups may lead to them being overlooked for other forms of microfinance programming.

There is a small but growing body of empirical studies done worldwide which have sought to demonstrate the impact of microfinance interventions on HIV prevention and care [14, 15, 17–20]. These studies have utilized a range of the microfinance strategies listed above, either introducing them individually or in combination with behavioral interventions for HIV-risk reduction (HIVRR). Several studies targeted FSW, including Project JEWEL in Baltimore, which provided training in craft-making to FSW who used drugs, and showed, on average, a decrease in the number of both sexual contacts and paying partners, as well as increased condom use [18]. Through a similar study in Chennai, India, FSW were taught tailoring skills, and saw a decrease in paying partners, as well as increased licit income [19]. A microenterprise intervention with FSW in Kenya’s urban slums, which offered financial literacy training and microloans, demonstrated an overall decrease in the number of sex partners and a higher consistency of condom use; furthermore, nearly half of participants stopped sex work altogether and two thirds developed operational businesses [20].

The majority of microfinance studies included a microcredit or loan component (both group and individual loans) to support small business development, or a vocational training component, but few have focused on asset-building. The Undarga study among street-based sex workers in Ulaanbaatar, Mongolia, is the first to have addressed this, using a randomized controlled trial (RCT) design to test the efficacy of a savings-led microfinance program in combination with HIVRR [17]. The benefit of savings-led interventions over microcredit interventions is that they enable participants to accumulate assets faster and pay for life events without accumulating debt and an over-reliance on microloans, for which interest rates can be onerous. This makes them less likely to cause additional financial strains for populations like FSW, which already face significant financial burdens. Participants in Undarga were randomized to receive either a four-session HIVRR intervention alone, or the same four-session HIVRR intervention and a savings-led microfinance program. The microfinance components included financial literacy training, a business development training with mentorship, and a matched savings program to help women establish small businesses. Findings showed that women in the microfinance arm reported significantly fewer unprotected sex acts at 6 months post intervention and that women in the microfinance arm reported a significantly lower percentage of income from sex work, increased odds of reporting no income from sex work, and increased odds that sex work was not their main source of income at 6 months post intervention compared to women who received HIV prevention alone [17, 21]. While women from both study arms reported a decrease in the number of paying sexual partners between the baseline and 6 months post-intervention assessments, those who had received the microfinance components reported a significantly larger decrease than those who received HIVRR alone [17].

While this study suggests the success of savings-led microfinance for HIV-risk reduction among FSW, gaps remain in the evidence base for microfinance for HIV-risk reduction among women who use drugs. The four studies detailed above are the only ones which have targeted female sex workers, and only one of these three targeted FSW who used drugs. Furthermore, past studies have assessed a limited range of outcomes, mostly self-reported sexual risk behaviors. No studies to date have used biological measures of HIV or other STIs in their assessments, and only one considered ART adherence as an outcome. Finally, only a few of these studies utilized a RCT design.

This paper presents the protocol for a study which tests a combination HIVRR and savings-led microfinance intervention. The study described here is adapted from the Undarga study protocol [17]. It responds to calls for more structural interventions for HIV focused on women who use drugs [22] and rigorous testing of HIVRR economic empowerment interventions through a RCT [13]. To the best of our knowledge, it is the only study to date to incorporate biological assessments, including testing for HIV and other STIs, and viral-load and CD4 biomarkers for those who are HIV positive. It is one of the few interventions that focuses on the key affected population of women at dual risk of HIV from both drug use and sex work. This study should have global as well as regional implications for structural interventions for HIVRR.

## Methods/design

This study uses a cluster randomized controlled trial (c-RCT) to evaluate a combination HIVRR and microfinance (MF) intervention among FSW who use drugs in Kazakhstan. The study compares two arms: a combination HIVRR+MF intervention treatment arm and a control arm, which receives the HIVRR component alone. The study assesses outcomes over a 15-month period, which encompasses up to 3 months of intervention activities, and 12 months of follow-up. Study recruitment and enrollment began in May 2015, and follow-up data collection will be completed in October 2018.

The theoretical framework for the study is shown in Fig. 1. The primary aim of the study is to test whether participants assigned to the combined HIVRR+MF condition have improved outcomes on a number of indicators, as compared to those assigned to the HIVRR condition. These indicators include: (1) a lower cumulative incidence of biologically confirmed STIs (syphilis, gonorrhea, trichomoniasis, chlamydia and mycoplasma), (2) a lower rate of new HIV and hepatitis C virus (HCV) cases, (3) a greater decrease in the number of unprotected vaginal and anal sexual acts and a greater increase in the proportion of protected sexual acts with both regular and paying partners, (4) a reduction in the proportion of unsafe injection acts for those participants who inject drugs, and (5) a lower proportion of monthly income from sex work. These outcomes are summarized in Table 1.

**Fig. 1 Fig1:**
[figure not shown]
Theoretical framework

**Table 1 Tab1:** Assessment variables

	Measurement	Timepoint^a^			
Moderators		B	M6	M9	M15
Age, income, education, marital status, experience of sex work, trauma	Sociodemographic Questionnaire	X	X	X	X
Substance abuse and criminal justice history	Modified Risk Behavior Assessment (RBA) [36]	X	X	X	X
Mental health status	BSI [37]	X	X	X	X
Partner violence history (paying and intimate)	Revised Conflict Tactics Scale [38]	X	X	X	X
Number and type of sexual partners (past year)	Modified RBA [36]	X	X	X	X
Perceived stigma	Modified Sex Worker Stigma (SWS) Index [39]	X	X	X	X
Mediators		B	M6	M9	M15
HIV/STI knowledge	HIV/STI knowledge [40]	X	X	X	X
Condom use self-efficacy	Condom Use Self-Efficacy Scale [41]	X	X	X	X
Condom use outcome expectancies	Condom Barriers Scale [42]	X	X	X	X
Condom negotiation self-efficacy	Condom Negotiation Self Efficacy Scale [43]	X	X	X	X
Sexual communication skills	Sexual Communication Scale [44]	X	X	X	X
Social support	MSPSS [45]	X	X	X	X
Current partner violence (paying and intimate)	Revised Conflict Tactics scale [38]	X	X	X	X
Access to services	RBA Services [36]	X	X	X	X
^b^Financial literacy	Financial literacy knowledge [46]	X	X	X	X
^b^Savings deposits	Bank Statements		X	X	X
^b^Vocational training sessions attended	Attendance/process		X	X	X
Outcomes		B	M6	M9	M15
STI (gonorrhea, syphilis, trichomoniasis, chlamydia, *Mycoplasma genitalium*), HCV, and HIV status	Laboratory assays (see Table 2)	X		X	X
Sexual behavioral risk: number and % of unprotected sexual acts	Modified RBA [36]	X	X	X	X
Number and % shared injection acts, other drug use	Modified RBA [36]	X	X	X	X
Proportion of income from sex work, savings, debt	Economic Indicators Questionnaire	X	X	X	X
Cost of staff time, supplies, overhead for HIVRR and for MF	Project records; Administration review	Ongoing			

^a^*B* baseline (prior to randomization or intervention); *M6* month-6 follow-up, *M9* month-9 follow-up, *M15* month-15 follow-up

^b^Uniquely associated with asset theory and the HIVRR+MF arm

*HCV* hepatitis C virus, *HIV* human immunodeficiency virus, *HIVRR* HIV relative risk, *MF* microfinance, *STI* sexually transmitted disease

Secondary aims of the study include an examination of how study outcomes are moderated by personal and structural characteristics, including sociodemographics, substance use history, criminal justice history, sexual history, etc. Secondary aims also include an examination of how study outcomes are mediated by several key, theory-driven variables, such as financial literacy knowledge and skills, HIV knowledge, condom use self-efficacy, se outcome expectancies, etc. In addition, a qualitative component will examine women’s personal reactions to each of the HIVRR+MF components, factors promoting the use of the intervention, and barriers that may impede their participation and the fidelity of intervention implementation. Finally, a cost-effectiveness component is included to estimate the costs and cost-effectiveness of the HIVRR+MF intervention on averted cumulative STIs, HCV, and HIV over the 12-month period.

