#### Vocational Training (VT)

During months 2 and 3 of the intervention period, the treatment arm receives the Vocational Training (VT) intervention component. VT provides technical education and skills-building in a craft or trade. Including VT as a component in the HIVRR+MF intervention arm allows participants to gain competence in an employable trade, which grounds the intervention in the real world for scale-up after the trial ends. Participants in the treatment arm decide whether they wish to be enrolled in hairdressing, sewing, or manicurist vocational training sessions (dependent on course availability at each study site). Our selection of these options was informed by local feedback and a feasibility pilot conducted prior to study start, which confirmed that these were considered growing small business targets for women and that high-risk women reacted favorably to this model of vocational training. These trainings are conducted by professionals, who work either individually in the community or through a school or training program. VT partner sites were selected based on the quality of their facilities, the availability of afternoon and part-time training hours to accommodate participant schedules, and a reputation for successful graduation and certifications among students. All treatment arm participants are eligible to attend VT sessions regardless of how many FLT sessions they attended, as the material presented in the VT sessions is unrelated to the FLT. Vocational training is provided three times per week over the course of 2 months, for 24 sessions. Tuition is free to participants and women attend in small groups with only their cohort peers. Participants receive small financial incentives (US$12) for sessions attended.

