#### Matched savings

From week 3 until the end of the intervention period at the end of month 3, the treatment arm receives the matched savings component of the intervention. The matched savings component of the HIVRR+MF intervention is also adapted from the Undarga program [17]. Building assets prior to shifting sources of income or moving to new or self-employment may increase the likelihood for increased income from other sources than sex work. As mentioned above, participants receive incentive payments (US$12/session) for each FLT or VT session attended. During the FLT intervention, participants receive support to open a personal savings account in a partner bank, and are encouraged to deposit their session attendance incentives in this account. Throughout the rest of the treatment intervention period, for every dollar of their incentive payment money deposited in their personal account, the project will deposit an equal amount in a separate, project-controlled account under the participant’s name. Participant’s funds will only be matched up to the total amount that they have received from incentive payments for session attendance – this limit ensures that women are not earning income through sex work for their matched savings. If a participant decides to save 100% of her incentive after every session, she will have saved a total of US$360 and would receive a matching US$360 for a total of US$720. Due to lack of documentation, lingering distrust of the banking system, or other barriers, some women may elect to never open a bank account. These participants have the option to store money with the program staff in an informal account until the time of withdrawal, and these informal accounts are also matched in a separate, project-controlled account under the participant’s name.

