
To examine whether key, theory-driven variables mediate the intervention’s effects on the primary outcomes, again we expand the logistic GEE modeling framework from the primary aim to examine (1) whether the HIVRR+MF improves the primary outcome compared to HIVRR alone; (2) whether the intervention improves each mediator; and (3) whether improvements in the mediator over time are associated with improvements in the primary outcome over time.

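### Savings deposits and vocational sessions attended are listed as mediators, but they are intervention dose in one arm without a baseline, so the planned mediation steps cannot test them

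*Protocol article*

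**What the plan says.** Table 1 (Assessment variables) has a block headed Mediators with eleven rows. Two of them are "Savings deposits", taken from bank statements, and "Vocational training sessions attended", taken from attendance records. Both are scheduled at months 6, 9 and 15 only. Both carry footnote b, "Uniquely associated with asset theory and the HIVRR+MF arm". Financial literacy carries the same footnote, but it is a knowledge score scheduled at baseline as well.

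The intervention sections confirm who can have these values. In months 2 and 3, "the treatment arm receives the Vocational Training (VT) intervention component", and "Vocational training is provided three times per week over the course of 2 months, for 24 sessions". From week 3, "the treatment arm receives the matched savings component of the intervention". The Process measures section records vocational attendance and matched deposits for the treatment arm.

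The mediation paragraph under Data analysis extends the primary logistic GEE to ask three things: (1) whether HIVRR+MF improves the primary outcome; (2) "whether the intervention improves each mediator"; and (3) whether mediator improvement over time goes with outcome improvement over time. It makes no exception for the footnoted variables and does not say whether arm stays in the step 3 model.

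Table 1 also has an Outcomes row, "Proportion of income from sex work, savings, debt", collected by questionnaire at baseline and months 6, 9 and 15 with no arm flag.

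**The concern.** A mediator analysis needs a variable that could move in either arm, so that the arm comparison of the mediator is a real question. The number of vocational sessions and the amount of project-matched deposits are the delivered intervention itself. Control women are not offered either, so their values are zero or not recorded.

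The Discussion presents the study of causal pathways and mediating variables as a contribution of the trial. If the arms differ and these two variables go through the three steps, the report could name savings or training as the mechanism when the data cannot show that. Such a statement could steer decisions on which components to scale up.

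**Working it through.** **Inputs from the article.** STI incidence 0.144 (HIVRR) and 0.043 (HIVRR+MF); two-sided α 0.05; power 80%; ICC 0.01; cohorts of six to eight; attrition 20%; 350 women randomised 1:1, so 280 completers; at most 24 vocational sessions.

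**The plan's own figure.** n per arm = [1.96·√(2·p̄·q̄) + 0.8416·√(p₁q₁ + p₂q₂)]² / (p₁ − p₂)². With p̄ = 0.0935 this is (0.8070 + 0.3413)² / 0.101² = 129.2, so 130. With cohorts of 7: 130 × (1 + 6 × 0.01) / 0.8 = 172.3, so 173 per arm and 346 in total. Cohorts of 6 and 8 give 342 and 348. The two incidences therefore reproduce 350 closely and are a fair basis for simulation.

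**Step 2.** Control value 0 by design; treated value between 0 and 24. The arm difference is positive as soon as anyone attends. It was significant in 100% of simulated trials in every scenario, so it carries no information.

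**Improvement over time.** Neither variable has a baseline in Table 1. Vocational training ends by month 3, so attendance is the same number at months 6, 9 and 15. There is no change to relate to outcome change.

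**Step 3, simulated for attendance.** 40 cohorts of 7, ICC 0.01, one binary outcome, exchangeable logistic GEE with robust standard errors, 400 trials per scenario. Attendance is 0 in controls and binomial out of 24 in HIVRR+MF, with each woman's log-odds of attending equal to 0.7 plus a standard normal. The attendance model, the single outcome and the 0.4 vs 0.2 rates are assumptions. Attendance has no effect on the outcome. A step counts as positive if p < 0.05 in the favourable direction.

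| Scenario | Step 1 | Step 3, no arm term | Step 3 without arm, given step 1 | All three, no arm term | Step 3, arm kept | All three, arm kept |
|---|---|---|---|---|---|---|
| 0.144 vs 0.043 | 84% | 73% | 85% | 72% | 5.8% | 5.2% |
| 0.4 vs 0.2 | 95% | 89% | 94% | 89% | 6.0% | 6.0% |
| 0.144 in both | 4.2% | 3.5% | – | 2.2% | 3.2% | 0.2% |
| 0.4 in both | 2.8% | 3.2% | – | 2.0% | 3.8% | 0% |

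Monte Carlo error is about 1.9 points on the 85% (√(0.854 × 0.146 / 336)) and 1.2 points on the 6%. Because only favourable results count, the exact reference for the arm-adjusted column is 2.5%. The excess is plausible with 20 treated cohorts and about 0.043 × 140 = 6 events in that arm.

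A separate simulation by ordinary logistic regression (140 per arm, 4,000 trials, 0.144 vs 0.043, no arm term) varied attendance. Step 3 was positive in 59% of trials with attendance uniform on 0–24, and in 79% with a mean near 18. Given a significant arm effect, all steps passed in 69% to 92%.

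**Step 3 with arm kept and engagement confounding.** Let an unmeasured trait raise attendance and lower the log-odds of the outcome by 0.5 per SD (assumed). The arm-adjusted step 3 is then falsely positive in about 60% of trials at 0.4 vs 0.2. Repeating the same simulation at 0.144 vs 0.043 with 1,000 trials gave about 28%, lower because events are few.

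**The case against.** A reader might infer that the whole mediation test is positive by construction, or that it will blame savings or training whenever the arms differ. The documents do not support that. Step 1 is empirical, and with no arm effect all three steps passed in only about 2% of trials. Even with a significant arm effect and no arm term, step 3 was not positive every time.

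The high step 3 rates also depend on leaving arm out, which the article does not say. The mediation models extend the primary framework, which contains arm, and the moderator models in the same section keep main effects. Keeping arm is a fair reading, and it brings the rate down to about 6%. Attendance is also not a copy of the arm indicator: if uniform on 0–24 in one arm and 0 in the other, the between-arm variance is 36 and the average within-arm variance is 52/2 = 26, so arm explains 36/62 = 58% (correlation 0.76).

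A reader might also infer that every control woman is at zero on savings. The article does not say so: control women can hold savings of their own, and bank statements may simply not be collected from them. The simulations cover attendance only. Nor can footnote b by itself mean absent in controls, since it also marks financial literacy.

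Finally, these are two of eleven mediators in a secondary aim. The text names neither as an example, and Process measures already treats both as treatment-arm data. An article may leave model detail to an analysis plan.

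All of this limits the size of the point. It does not remove it: the article itself gives the two variables the mediator role and fixes the steps applied to each mediator. Stating that arm is kept cures the built-in association, but not the automatic step 2, the missing baseline or the self-selection.

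**Conclusion.** The point holds in a limited form. For vocational sessions and project-matched deposits, step 2 is satisfied by design, and neither variable has a baseline from which to measure improvement. Step 3 has two readings, and neither gives a valid mediation result. Without arm, it mostly repeats the arm effect (about 85% positive given a significant arm effect at the plan's incidences, with no true attendance effect). With arm, the false-positive rate is close to nominal if attendance is unrelated to prognosis. What is then tested is a non-randomised dose-response within HIVRR+MF, open to confounding by engagement (28% to 60% false positives under the assumed trait).

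The percentages rest on assumed attendance distributions, a single binary outcome and an assumed confounder strength, and none of them applies to savings deposits. The facts about step 2 and the missing baseline rest on the article alone. The primary comparison and the other nine mediators are not affected by this defect.

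**What to change.** 1. Take savings deposits and vocational sessions attended off the between-arm mediator list in Table 1. Report them as uptake within HIVRR+MF, labelled exploratory and non-randomised, with any association with outcome adjusted for baseline predictors of engagement.
2. State in the mediation paragraph that arm stays in the step 3 model.
3. Restrict formal mediation of the asset pathway to variables scheduled in both arms at baseline and months 6, 9 and 15. The financial literacy score qualifies; add a note that it carries footnote b but can vary in both arms. Questionnaire savings and debt could serve as exploratory mediators, with a statement that Table 1 now lists them as outcomes.

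The cost is a small change of analysis wording. No new data are needed. The trial gives up a formal mediation claim for the two variables.
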